# The Femina collaboration and projects

The Fetal Movement Intervention Assessment (Femina) collaboration engages several researchers worldwide with different aims and approaches.

Fetal activity serves as an indirect measure of central nervous system integrity and function, and regular FM can be regarded as an expression of fetal well-being1;2. Pregnancies in which the mother report decreased fetal movements (DFM) may indicate danger for the fetus2;3, and is associated with adverse outcomes as fetal hypoxia, growth restriction, preterm birth and stillbirth4-7. The unborn child responds automatically to hypoxia by redistributing blood flow away from the non-essential organs8 and reduction of non-vital activities9; *movements*. DFM is experienced by 4-15% of all pregnancies3;4.

Femina started in May 2004, with registration of the women seeking to 14 Norwegian hospitals for their worry because of DFM. Another 14 hospitals are participating in the UK, USA, Australia and New Zealand. The overall aim is to improve pregnancy health, pregnancy outcomes and child health through better understanding, awareness and management of fetal activity in general and DFM in particular. This include improving knowledge and clinical management through 1) Learning their epidemiology and outcome, 2) Improving the quality of care by health professionals, 3) Improving maternal information and vigilance, 4) Exploring the basic associations between fetal activity and outcome, 5) Testing new and improved approaches to fetal movement counting and 6) studying fetal growth and placental pathology in pregnancies with DFM.

The literature describes inconsistent and overmedicalized policies regarding the identification, assessment and monitoring of DFM3;10;11. There is a lack of evidence based knowledge of “normal” vs. “abnormal” fetal movements. Apparent “limits of normality” are mostly based on high risk pregnancies and concepts of DFM4;12. Femina has documented a wide spread of the health professionals’ view on FM’s relevance and significance as a marker for fetal well-being11, and there are large variations in management when women present their concern because of decreased fetal movements, how, and to what extent these risk pregnancies are identified in the population3. None of the hospitals involved in Femina in Norway had written guidelines before Femina started. They have however, responded to this sub-standard situation by consensus-driven quality-improvement projects starting in November 2005 on the two issues that need to follow each other – information to women and in-hospital management.

Femina has prospectively collected a population-based cohort of more than 5500 cases from about 82 000 pregnancies. Preliminary results from Femina have shown significant possibilities for clinical quality improvements with regard to *management* in pregnancies with DFM and *maternal perception* to fetal movements. Our results show that most mothers in our population did interpret their baby’s FM as a sign of good health, but that what they considered a reason for concern varied greatly – ranging from concerns because their baby kicked less than their friends baby (17%), to not contacting health professional even with total absence of FM (unpublished), and the few that actually contacted health professionals frequently receive non-productive or even dangerous information, ranging from telling the mother that she should feel 25 kicks/hour, to “reassurance” that it is only DFM after total absence of FM for over 24 hours11. In our Norwegian population, 50% waited more than 24 hours without any FM before they contacted health professionals. They did not understand the urgency and severity of this sign. When finally contacting help, they received variable help, as management consumed considerable health resources without any guidelines or monitoring of outcomes3;11. With lacking information to health professionals and pregnant women, as much as 50% of women affected by stillbirth perceive a reduction of FM, in many cases for several days before death4;5;13-15.

# Effects of fetal movement counting – a multi centre randomized controlled trial

## The current situation in the population to study

Before the studies included in Femina, there have been no randomized controlled trials of any aspects of management of DFM or on effective information to pregnant women. This situation yields unique opportunities to study the significance of DFM in depth, and also to approach one of the more controversial issues in antenatal care; the formal use of kick charts for total populations. Several case-control studies and one small Danish randomized controlled trial have indicated that the use of kick charts could significantly reduce stillbirths16. The only large randomized controlled trial compared kick charts for all women versus kick charts for all risk pregnancies in the population17. While the stillbirth rate in their population fell significantly during the study period with high vigilance and awareness among both pregnant women and health professionals (despite the failing management of DFM where 10% died in hospital due to clinical error), they failed to show significant differences between the groups.

There is little controversy in that pregnant women should be informed and guided to understand the significance of significantly decreased or absent fetal movements, and little controversy that they should receive a basic evaluation when presenting with symptoms. Yet the question remains – should all women use a formal kick chart? Does it really represent a helpful tool to increase their vigilance or their ability to distinguish pathology from normal variation? Does it promote maternal-fetal attachment? Is it harmful? Is it stressful? Does it cause an unneeded increase in the use of health services, or does it help provide better care to those who need it?

## Maternal ability to identify significant changes in fetal activity level

Maternal perception of FM is influenced by several factors; gestational age, type of fetal movement, maternal position, obesity, parity, placental location and psychological factors18. Several reports have stated that subjective registrations and assessments of decreased fetal activity might be useful in preceding many pregnancies with adverse outcomes2;4;19;20. Valentin has described a great interindividual variability in fetal activity and a small intraindividual variability12 and the most important current identifier of DFM is the women’s perception of what is a decrease of FM12. DFM reported by the mother in the week prior to delivery, has showed to be a statistically significant prognosis of fetal wellbeing, with a sensitivity of 57.7% and 56.5% for predicting alterations in fetal tests in normal and pathologic pregnancies and a specificity of 96.2% and 88.0% for normal and pathologic pregnancies respectively20.

The medicalization of perinatal care may have affected pregnant women’s view on own ability to recognize warning signals. However, the past several years, it seems to be an ongoing process against the medicalized perinatal care, and governmental reports in several countries have advised that women should be enabled to make and implement informed choices and the mothers have been increasingly encouraged to take an active part in making decisions regarding their care. In line with guidelines for antenatal care from WHO21 and NICE22, the new Norwegian guidelines for standard antenatal care also focus on demedicalization of pregnancy; with reduced frequency of standard antenatal controls and less tests23. Demedicalization in antenatal care implies to give the power back to the women, stimulate her listening to her body’s signals and improve the trust in non-instrumental signals. However, there seems to be a “missing link” – women are recommended fewer standard controls, but *without* receiving information and tools to be left with this responsibility. The mothers have not given relevant tools to be able to take care for their unborn child. This may affect their reporting of DFM and consequently time-consuming and frequently unnecessary investigations. We want to develop scientific knowledge on the pregnant women’s perception of FM and interpretation of significant changes in the FM pattern. Information and FMC could be a tool for getting to know their unborn child better, give the mothers a greater sense of control of her pregnancy and improve their ability to act on signs of complications at an optimal point of time.

The basic principle for antenatal care is to identify risk conditions where further observation or intervention is indicated in order to improve health for the mother or the child. An intervention may therefore be a positive action, e.g. if a CS is performed after a mother has experienced DFM and the child was in a threatened condition. Therefore, this study aims will be the number of identified risk pregnancies, not the end point of the pregnancies.

## Fetal movement counting – advantages and disadvantages

Maternal perception of fetal movements has, over the years, become recognized as a valuable tool for early detection of fetal compromise. The rationale for fetal movement counting is that adverse pregnancy outcome can be prevented by acting immediately when the woman reports decreased fetal movements. However, the importance of FMC in assessing fetal well-being is controversial. FMC is simple and can be done at home. It is economical, as there are no human or material resources needed, but it does intrude on the woman’s time. FMC might reduce fetal death and asphyxia by precipitating timely intervention, but on the other hand, it might increase obstetric interventions and prematurity. It is important to establish whether in practice benefits outweighs risks or vice versa, both as a routine procedure and in selected high-risk pregnancies, confirmed in a Cochrane review. This review conclude that there is a lack of knowledge about the sensitivity and specificity of FMC; its effectiveness in decreasing the perinatal mortality in high-risk and low-risk women; its acceptability to women; how easy it is for women; and the best fetal movement counting method24.

Several methods for monitoring fetal movements have been used; the two most common are “daily movement count”19 or “count-to-ten”25, the latter has been found to be most user-friendly26;27. The Femina collaboration has chosen a modified “count-to-ten”-method; the mothers are asked to note the time it takes to feel 10 movements after she have felt one movement; counting will start when the baby is awake. This method reduces the normal variations, since the counting period not will start when the baby is sleeping. With a focused counting according to this method, the average pregnant woman in the third trimester will perceive 10 FM within 20 minutes, but only after two hours it is a rare event11;28;29.

## Effects on the women’s feeling of well-being

Psychological changes as a result of attention to fetal activity could be negative or positive. FMC might increase anxiety or might be reassuring. Studies evaluating use of FMC, have shown that FMC raised maternal anxiety levels17;30, but others did not find any association with anxiety31-33. Even if Grant & al17 found FMC as having a little, if any, stress inducing effects on women, they suggested that any maternal anxiety experienced is a reflection of more general concern about FM rather than concern prompted by formal counting. They also argued that stress and anxiety were significantly reduced when feedback of information was given to women regarding the health of their baby. Information and instructions are essential in clinical use of FMC12, and communication is seen as vital between the women and the providers of antenatal care for anxiety to be successfully allayed in women using a fetal movement counting policy. The Grant-study showed that FMC gave the mothers a non-significant increase in confidence and control17. Mikhail & al found better attachment between mother and child and slightly decrease in feelings of wellbeing for those who counted34.

Fetal movement counting itself will not reduce the likelihood of adverse pregnancy outcome. This will happen only if both women and caregivers respond adequately to the signals of decreased fetal activity. More observant women are not equal with more concerned women. In many cases, an adequate level of concern may also be warranted, versus a lack of vigilance putting their pregnancy at risk. Maternal individual responsibility is desirable. FMC may have positive effects on recognizing pregnancies at risk. However, it can also induce mental non-wellbeing, like anxiety, stress, irritation, tiredness, feeling guilty if not practicing FMC, or it may intrude in other activities for the mother or in other ways affect her quality of life. These aspects remain unknown and will be one of the aims of this study.

## Maternal-fetal attachment

The concept of maternal-fetal attachment (MFA) has been used in different ways with different theoretical frameworks to describe the relationship between a pregnant woman and her fetus. The research on prenatal attachment is characterized by low validity, including inadequate operational definitions of the construct, small, homogenous samples, and a lack of sensitivity to cultural issues35. It is a lack of knowledge on the processes by which MFA develops, including physiological and psychological mechanisms that could shape the development of MFA, and there is a lack of knowledge on what constitutes “normative” scores36, even if Condon in two old studies has estimated that about 8 to 15 per cent of women develop minimal attachment to their child37;38.

Maternal feelings and sensitivity to her child develop along a continuum throughout pregnancy as a result of dynamic psychological and physiological events39. A broad spectrum of MFA has been observed during pregnancy. The rate and degree of MFA development appears to be influenced by gestational age at quickening, amount of fetal movements, pregnancy history and the mother’s own attachment history. Fetal movements, ultrasound images, the delivery, the baby’s first smiles, are all opportune moments to consolidate the desire for the infant40. Development of MFA is heightened by fetal movements41. The development of MFA is rooted in the desire to have a baby. An unplanned pregnancy or an unwanted baby may compromise the parent-infant attachment42. It is assumed that the MFA is relatively stable when the women have reached their individual level, this is reported to develop in particular in the second trimester43.

Attachment theories state that the affectional tie between a mother and her infant is essential for enhancing the child’s early survival and later capacity for getting along with others34. Associations between prenatal and postnatal attachment have been anticipated through many years, but there have been inconsistent findings; some studies have failed to report any significant association between prenatal and postnatal attachment35;39, others have identified associations between pre- and postnatal attachment44. Maternal prenatal attachment during the third trimester of pregnancy is associated with the postnatal maternal involvement, and can serve as an important diagnostic aid in identifying those women for whom the mother-child interaction is likely to be sub-optimal45. Women intending to breast feed had higher level of maternal fetal attachment46. It has been assumed that a healthy attachment between mother and the unborn babies is supposed to continue to be a good, sensitive interaction postnatally43. A child’s secure attachment to the mother is positively correlated with the child’s exploration ability, problem-solving ability, curiosity and control in the preschool years47 and strong prenatal attachment may decrease the risk of child abuse48.

Maternal mood state has been consistently related to ratings of MFA49; prenatal depression had a negative relationship to MFA, and MFA a positive relationship with positive prenatal health practices of the pregnant woman that may affect her health, the health of the fetus or the pregnancy outcome, like diet, sleep, exercise, abstaining from harmful substances, such as alcohol, cigarettes or drugs and prenatal care. However; positive MFA may mediate the negative effects of depression on positive health practices49. The technological development in western nations over the past 30 to 40 years has changed conceptions about pregnancies and the fetus. Women can detect pregnancy earlier and are able to view high-resolution images of their fetus at earlier dates. This knowledge may serve to allow women to adopt optimal health practice earlier.

Inconsistent findings on factors affecting the MFA are the reason for including elements of self-efficacy and self-esteem in the surveys. General self-efficacy is the belief in one’s competence to cope with a broad range of stressful or challenging demands50. Self-esteem is regarded as a stable personal trait51. Identification of low self-efficacy and self-esteem prior to FMC is important to assess possible interactions with MFA.

Since fetal movements is found to be the factor that increase the MFA, FMC be a tool for the mothers that might increase or decrease the their positive feelings toward the pregnancy and infant and stimulate to increased attachment between mother and child.

# Aim and outcome measures

The aim is to test effects of using formal kick counting chart in the third trimester of pregnancy in an unselected population. The research questions are:

Does Fetal Movement Counting:

1. Improve the identification of risk pregnancies / pathology?

*Primary outcome measures*: Numbers of identified pathological conditions in pregnancies (fetal growth restriction (FGR), acute caesarean section on fetal indication/non–reactive non-stress test (NST), oligohydramnios, pathologic blood flow in arteria umbilicalis, maternal perception of absent fetal movements for more than 24 hours before admission to hospital, or perinatal death).

*Secondary outcome measures*: Frequency of consultations because of maternal concern, use of resources in evaluation of these pregnancies (NST, ultrasound, Doppler, recurrent consultations), induced or spontaneous start of delivery, mode of birth.

1. Affect the women’s well-being?

*Primary outcome measure*: Maternal concern.

*Secondary outcome measure:* Maternal satisfaction with use of FMC and sense of control in interpretation of signals from own body and child.

1. Stimulate maternal-fetal attachment antepartum?

*Primary outcome measure*: Maternal-fetal attachment.

*Secondary outcome measure:* Health promoting behavior in pregnancy (smoking habits, use of alcohol, attending standard program for antenatal care).

# Methods of data collections

## Study design

Randomized controlled trial with women which respectively will:

a) Be given written information about fetal activity and instructions how to use and interpret FMC-charts – the intervention group

b) Follow standard antenatal care according to the Norwegian Guidelines – the control group

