## Recruitment of responders and data collection

Women will be recruited from the hospitals’ lists over women having been at the ultrasound screening in pregnancy week 17-19. A flow chart over data collection is appended (Appendix 1). All women will receive a letter in pregnancy week 23-24, asking to participate in a study of attitudes during pregnancy with a random possibility to be asked to perform FMC in the third trimester. Mothers, who agree to participate, do this by signing an informed consent and completing a baseline questionnaire (QI). On completion of the baseline inventories, but before inspection of the results, an assistant will perform the randomization into the FMC-group and the control group.

Women in the FMC-group will be asked to count fetal movements daily from gestational week 28. These women will be telephoned one week after commencement, to discuss questions or problems with the charting technique. Women in the control group will be told about the next survey at 34 weeks of gestation. Women in both groups will be asked to perform prospective, structured registrations – like a diary - if they were concerned about DFM and return these diaries to the study group after the delivery.

The questionnaires will be distributed in pregnancy weeks 24 (questionnaire I) and 34 (II). Answering the questionnaires can be done either by paper or by web-pages with interactive questions. An appropriate web-solution will be used for electronic data collection. Alternative retrieval for paper version: Scanning of questionnaires at the NIPH.

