# Time schedule

| **Data-collection/focus** | **Started/estimated started** | **Estimated to be finished** |
| --- | --- | --- |
| Preparation of the studies | Sept 06 | April 07 |
| RCT: information versus fetal movement counting | Recruiting respondents: May 07 | December 07 |
| Data analyses: January 08 | January 09 |
| Publication of four scientific articles |  |  |
| 1) Maternal perception of fetal movements in a total population – two cross-sectional surveys |  | June 07 |
| 2) FMC and identification of perinatal risk factors |  | March 08 |
| 3) FMC and maternal concern |  | October 08 |
| 4) FMC and maternal-fetal attachment |  | January 09 |

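### The aim names the kick chart, but the arms also differ in written information and a support call, so the trial estimates a package and cannot isolate the chart

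*Protocol*

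**What the plan says.** - **Motivating question** (Protocol, The current situation in the population to study). Informing women about reduced or absent movements is presented as largely uncontroversial. What is left open is "should all women use a formal kick chart".
- **Aim** (section Aim and outcome measures). It is put in one sentence: "The aim is to test effects of using formal kick counting chart in the third trimester of pregnancy in an unselected population". Each of the three research questions then asks what fetal movement counting does: to identification of risk pregnancies, to well-being and to attachment.
- **Arms** (Study design). Women in the intervention arm will "Be given written information about fetal activity and instructions how to use and interpret FMC-charts". Women in the control arm will "Follow standard antenatal care according to the Norwegian Guidelines".
- **Call** (Recruitment of responders and data collection). Of the counting arm only: "These women will be telephoned one week after commencement, to discuss questions or problems with the charting technique". Ethics and applications gives the purpose as compliance and correct understanding of the counting instructions.
- **Common to both arms.** Both are asked to keep a diary if concerned about decreased movements, and all participants may contact the study group.
- **Label** (Time schedule). "RCT: information versus fetal movement counting".

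**The concern.** The protocol describes three different comparisons. The aim implies chart against no chart. The Time schedule label implies information against counting, that is, a comparator that has been informed. Study design sets information plus chart, with a call added, against standard care without the study information.

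The difference matters because the question to be answered is whether all women should use a chart, given that informing them is already accepted. If the counting arm identifies more risk pregnancies, the leaflet may account for some or all of it. If maternal concern does not differ, the effects of information and counting may have offset each other; that is possible, though nothing in the protocol shows it. In either case a conclusion for or against the chart itself would go beyond what the two arms can show. A statistical analysis plan could not repair this, because it follows from what each arm receives.

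**Working it through.** No figure in the protocol decides this point, so the check is mainly a comparison of sections.

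**1. What differs between the arms**

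| Component | Counting arm | Control arm | Protocol section |
|---|---|---|---|
| Written fetal-activity information | yes | not provided for | Study design |
| Chart, instructions, daily counting from week 28 | yes | no | Study design; Recruitment of responders and data collection |
| Call one week after start | yes | no | Recruitment of responders and data collection; Ethics and applications |
| Diary if concerned about decreased movements | yes | yes | Recruitment of responders and data collection |
| Invitation to contact the study group | yes | yes | Ethics and applications |

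The last two rows are the same in both arms and cannot explain a difference between them.

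**2. What the comparison identifies**

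Write Y(i,c) for the mean outcome with information i and counting c (1 = given, 0 = not given), treating the call as part of delivering counting. The trial estimates

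Y(1,1) − Y(0,0) = [Y(1,1) − Y(1,0)] + [Y(1,0) − Y(0,0)].

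The first bracket is counting added to information, which is the question the background leaves open. The second is information alone. Only the sum is estimated, because no arm receives information without counting.

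**3. Whether the second bracket could matter**

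- The Femina collaboration and projects reports that 50% of women waited more than 24 hours without any movement before making contact, and puts this down to not grasping how serious the sign was. Absence for more than 24 hours before admission is a component of the first primary outcome. Written information could change when women present, without a chart.
- That component is small. The table under Power analyses gives it a prevalence of 0.5% within a compound of 13.52%. This is 0.5 / 13.52 = 3.7% of the compound, or 538 × 0.005 = 2.7 women per arm. It shows that information could act on the outcome, not that it would dominate.
- Standard care is unlikely to supply the same information. The section on maternal ability to identify changes says women now have fewer routine visits and are not given the information and tools to go with them. Sample recruits outside the existing Femina hospitals, where work on informing women had begun, and aims to limit the spread of information between participants.
- The protocol itself treats information and counting as distinct: it has separate questionnaire sections on each. The section on information does not say which arm is asked, but no section assigns the information to controls.

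**4. What informing both arms would cost in power**

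Inputs from Power analyses: concern, difference 0.12, SD 0.65, 462 per arm; attachment, difference 5, SD 10.2, 64 per arm; planned size 538 per arm. Two-sided 0.05, 80% power.

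- Concern: n = 2 × (1.96 + 0.842)² × 0.65² / 0.12² ≈ 461 per arm (stated 462).
- Attachment: n = 2 × (1.96 + 0.842)² × 10.2² / 5² ≈ 66 per arm (stated 64).

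Power at 538 per arm is Φ(s × δ × √(538/2) / SD − 1.96), where s is the share of the planned difference due to counting. The shares are assumptions; the protocol gives none.

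| Share s | Concern | Attachment |
|---|---|---|
| 100% | 86% | about 100% |
| 75% | 62% | about 100% |
| 50% | 33% | 98% |
| 25% | 11% | 52% |

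These figures assume that information and counting act in the same direction. If they pull concern in opposite directions, informing both arms could enlarge the contrast.

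**The case against.** The strongest reply is that counting cannot be delivered without information. The section on effects on women's well-being calls information and instructions essential when counting is used clinically, so a pragmatic trial of counting as it would be offered, against usual care, is a legitimate answer to a policy question. This stands. It defends the design, but not an aim and a label that describe something else: if information is integral, the aim should say so.

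The call is also mostly delivery of counting, since it is confined to charting problems and compliance. It is extra contact in one arm, but a weak rival explanation. The written information is the clearly separable component.

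The Time schedule label may be loose shorthand. Even so, read as written, it names a comparator that the protocol does not provide.

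Stronger readings are tempting, and the protocol does not support them:

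- **A reader might infer that no result can be credited to the intervention.** Randomisation gives a valid estimate of the package against standard care. Only a claim about the chart alone is out of reach.
- **A reader might infer that the diary undermines the contrast.** It goes to both arms. It only means that the comparator is standard care plus a diary for women who become concerned.
- **A reader might infer that the background proves information lowers anxiety.** The finding it cites concerns feedback on the health of the woman's own baby, not a general leaflet. Likewise, the 0.74 under Mother-child attachment is a correlation with perceived support from care providers, not an effect of a study call.

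**Conclusion.** The point holds as a mismatch between the stated aim and the arms. The aim, research questions and motivating question concern the chart or counting. The arms compare counting, written information and a charting call with standard care without the study information. The Time schedule label fits neither. The package effect is validly estimated, but the chart's share of it cannot be separated from that of the written information.

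The size of the information effect cannot be stated: the protocol gives no figure, and the shares used above only illustrate the cost of a different design. The conclusion assumes that standard care at the recruiting hospitals does not already supply equivalent information. The protocol's background supports that assumption but does not measure it. The matter is worth correcting because it governs what the trial may conclude. It is not a reason to regard the randomised comparison as invalid.

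**What to change.** Reconcile Aim and outcome measures, Study design and Time schedule:

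1. Restate the aim, the three research questions and the conclusions planned for the papers as the effect of fetal movement counting delivered with written fetal-movement information and a support call, compared with standard antenatal care.
2. Replace the Time schedule label with the same description.
3. State that no claim will be made about the chart alone.

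This costs only wording and leads to a narrower claim.

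An optional design alternative is to give both arms the same written information, which would isolate counting and its support. It is a trade-off, not a required change. It would probably shrink the contrast, and on the assumed shares power for maternal concern would fall from 86% to 62% (75% share) or 33% (50% share), while attachment would keep 98% at a 50% share. I give no such figures for risk identification, because the protocol does not say whether its 10% increase is relative or absolute.
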